# Effects of virtual rehabilitation versus conventional physical therapy on postural control, gait, and cognition of patients with Parkinson’s disease: study protocol for a randomized controlled feasibility trial

**DOI:** 10.1186/s40814-017-0210-3

**Published:** 2017-12-06

**Keywords:** Parkinson’s disease, Postural balance, Gait, Physical therapy modalities, Video games

## Abstract

**Background:**

There is an association among postural instability, gait dysfunction, and cognitive impairment in subjects with Parkinson’s disease (PD). Difficulty in dividing attention, response inhibition, and visuospatial attention deficiencies may contribute to the impairment of motor performance during daily activities. There are strong evidences that physical therapy can prevent physical and cognitive decline in individuals with PD. Recently, the European Physiotherapy Guideline (EPG) was developed based on randomized clinical trials about the effectiveness of the physical therapy to improve the functional deficiencies of individuals with PD. The EPG did not include the use of promising new intervention as virtual reality in PD due the lack of studies about its safety, feasibility and effectiveness. Therefore, this study protocol had as objective to evaluate the feasibility, safety and effectiveness of a physical therapy program-based on the European Physiotherapy Guideline (EPG) compared to Kinect-based training on postural control, gait, cognition, and quality of life (QoL) of Individuals with PD.

**Methods/design:**

A single-blind, parallel, randomized, controlled feasibility trial will be conducted with a sample of 32 individuals diagnosed with idiopathic PD. Participants will be allocated into control group (CG) and experimental group (EG). The intervention of the CG will be conventional physical therapy, and the intervention of the EG will be a supervised practice of five Kinect games. Both groups will perform 14 sessions of 1 h each one, twice a week over 7 weeks. Process outcomes will be safety, feasibility, adherence, and acceptability. Safety will be assessed by the proportion of participants who experienced intervention-related adverse events or any serious adverse event during the study period. Feasibility will be assessed through the scores of the games recorded in all training sessions. Adherence will be assessed through the participant’s attendance. Acceptability will be the motivation of the participants regarding the interventions. Clinical outcomes will be (1) postural control, (2) cognitive function, (3) balance, (4) gait, and (5) QoL. Individuals will be assessed pre- and post-interventions and after 30 days by a blinded evaluator.

**Discussion:**

This protocol will clarify if an intervention based on Kinect games will be feasible, safe, and acceptable for individuals with PD compared to conventional physical therapy. We will verify whether the proposed interventions can improve clinical outcomes as postural control, gait, cognition, and QoL of individuals with PD. Our hypothesis is that both Kinect games and conventional physical therapy will be feasible, safe, and acceptable for individuals with PD and will promote positive clinical effects. The results of this feasibility study will be used to design a future definitive clinical trial.

**Trial registration:**

Unique identification number in WHO Trial Registration: U1111-1171-0371. Brazilian Clinical Trial Registration Number RBR-27kqv5, registration date: February, 2016.

**Electronic supplementary material:**

The online version of this article (10.1186/s40814-017-0210-3) contains supplementary material, which is available to authorized users.

## Background

The impairment of gait, balance, and cognition of individuals with idiopathic Parkinson’s disease (PD) [1] increases the incidence of falls and impairs daily living activities [2]. Physical therapy can decrease the deleterious effects of PD that are resistant to dopaminergic replacement, such as festination, hesitation, freezing of gait, axial motor dysfunctions, and falls [3–6]. Based mainly on the finds of randomized clinical trials, the European Physiotherapy Guideline (EPG) for PD was developed and updated by specialists [7, 8]. There is strong evidence that physical therapy through different strategies can improve motor and cognitive functions of individuals with PD [9–13].

Practice-oriented task approach is recommended to facilitate the motor learning process and transferring for daily living activities [5–7]. The cue strategies can be used to improve gait, and specific exercises can improve balance [5, 6, 8].

Besides the well-consolidated conventional physical therapy, new therapeutic strategies based on practice-oriented task approach and visual and auditory feedback have shown positive effects on PD, among them the virtual reality training through video games [9, 10]. There are some studies suggesting that video games can promote integrated motor-cognitive training with the potential to improve balance, motor learning, cognition, and independence on daily living activities of individuals with PD [9, 11–13]. Through video games, individuals may be able to perform complex tasks (fast and large movements involving the whole body, rather than performing the movement in a single joint). Besides this, video games provide auditory and visual feedback that can contribute to physical performance [14, 15].

Amid recent technological advances, the Microsoft Kinect sensor (Kinect) is a potential low-cost alternative resource that can benefit in the treatment of individuals with PD. Pompeu et al. [16] assessed the safety and feasibility of Kinect games for individuals with PD in a pilot study with a small sample (*n* = 7) and without a control group. Due to the methodological issues of the pilot study of Pompeu et al. [16], a more robust randomized clinical feasibility trial is needed to clarify the safety and feasibility of the Kinect games compared to a conventional intervention.

The objective of this study will be to evaluate the safety, feasibility, adherence, acceptability, and clinical outcomes (postural control, gait, cognition, and QoL) of the Kinect game-based intervention compared to conventional physical therapy in individuals with PD. We hypothesize that the Kinect games will be feasible, safe, and acceptable and will provide improvements in the postural control, gait, cognition, and QoL of individuals with PD.

## Methods/design

### Trial design

This study will be a single-blind, parallel-group, randomized controlled feasibility trial. Participants will provide written informed consent prior to taking part in the study. The protocol will follow the CONSORT guidelines for reporting of non-pharmacological interventions.

The study was approved by the Ethics Committee of the Institute of Psychology, University of São Paulo, Brazil, number 1.506.842, and registered in ensaiosclinicos.gov (RBR-27kqv5). The current study was developed based on Standard Protocol Items: Recommendations for Interventional Trials (SPIRIT) (Additional file 1).

### Study setting

The study will be conducted in three different settings: (1) Motor Behavior Laboratory, School of Physical Education and Sports, University of São Paulo, Brazil; (2) Laboratory of Study and Research in Rehabilitation of Body Balance and Social Inclusion, Anhanguera Educational, São Paulo, SP, Brazil; and (3) Movement Disorders Unit, Federal University of São Paulo, São Paulo, SP, Brazil.

### Participants

#### Inclusion criteria

Individuals diagnosed with PD living in the city of São Paulo (Brazil) will be recruited. It will select individuals who meet the following inclusion criteria: 50–80 years of age, idiopathic PD diagnosed according to the criteria of the UK Brains Bank Parkinson’s Society [17], without clinical fluctuation, and in stages I to III of the modified Hoehn and Yahr [18]. All individuals should be treated with levodopa and/or their synergists. Moreover, they should be able to walk independently with or without assistive device and without signs of cognitive decline, defined according to the cutoff scores of the Mini Mental State Examination (MMSE) [19], adjusted according to the educational level (> 20 for illiterates, > 25 for individuals with 1 to 4 years of education, > 26 for individuals with 5 to 8 years, > 28 for individuals with 9 to 11 years, > 29 for individuals with more than 11 years of education) [19].

#### Exclusion criteria

It will exclude individuals with biomechanics, and significant cardiovascular or respiratory alterations that could compromise training performance. All individuals should be in medical treatment, and any clinical fluctuation reported at their medical records will be excluded.

### Procedure

Figure 1 outlines the study phases. Participants in both groups will be allocated to an intervention at the ratio of 1:1. The trial will be carried out over a 7-week period.

**Fig. 1 Fig1:**
[figure not shown]
Flow diagram of trial design. Abbreviations: PD Parkinson’s disease, HY Hoehn and Yahr, MMSE Mini Mental State Examination, n number of participants

### Outcome measures

Individuals will be evaluated during the “on” period by two blinded, trained physical therapists. The evaluators will be blinded to the type of intervention that individuals will receive. Individuals will be oriented to not comment to the evaluators about any details of the intervention that they will receive. In compliance with the pharmacodynamics of levodopa (onset is 20 to 40 min and duration of effect is 2 to 4 h after medication), individuals will be evaluated in the period of 2 h after medication, according to Lipp et al. [20]. This is the time at which the individual had better engine performance related to the effect of levodopa.

Table 1 details the outcome measures that will be used to assess the treatment effects. All measurements will be taken at baseline (week 0), at the end of the intervention (week 7), and 30 days after the second evaluation (follow-up). For a month after the intervention, the individuals will be instructed to not begin any new physical activity in order to not interfere in the evaluation of the long-lasting effects of the intervention.

**Table 1 Tab1:** Summary of the outcome measures to be used in the study design

Outcome	Measurement tool
Primary outcomes	
Center of pressure and limits of stability	Posturography through the Balance Rehabilitation Unit
Secondary outcomes	
Postural control	Mini Balance Evaluation Systems Test
Functional mobility	Dynamic Gait Index and Functional Gait Assessment
Physical functioning	Five Times Sit-to-Stand Test and 10-Meter Walk Test
Cognition	Montreal Cognitive Scale
Quality of life	Brazilian version of the Parkinson’s Disease Questionnaire

Scales that will be used in the study protocol

#### Process outcomes

Process outcomes will be safety, feasibility, adherence, and acceptability. Safety will be assessed by the proportion of participants who experienced intervention-related adverse events or any serious adverse event during the study period. An adverse event was defined as any untoward medical occurrence, such as falls, joint and muscular pain, syncope, dizziness, or any other medical condition that requires hospitalization or leads to disability.

Feasibility will be assessed through the scores of the games recorded in all training sessions, according to Pompeu et al. [16]. An increase in scores will indicate that the participant is able to not only play but also improve his performance in the games. To determine the adherence, we will collect each participant’s attendance records before and after the training sessions. We will conclude that the exercise program is feasible if we obtain > 50% attendance of all sessions per patient and a mean of attendance > 80% per session.

The acceptability will be evaluated through a questionnaire developed by the researchers of this study in which the individuals will answer questions related to their motivation to be involved in the intervention.

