### Adverse effects of the intervention

Adverse events are defined as any sign of pain perceived by the participants due to the training protocol lasting for 2 days or more. In addition, the occurrence of fall or injury to other body parts during training sessions will be considered as adverse effects. Falls are defined as “an unexpected event in which the participants come to rest on the ground, floor, or lower level” [29].

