## Discussion

This protocol will clarify whether an intervention based on Kinect games will be feasible, safe, and acceptable for individuals with PD compared to conventional physical therapy. We will verify whether the proposed interventions can improve clinical outcomes as postural control, gait, cognition, and QoL of individuals with PD. Our hypothesis is that both Kinect games and conventional physical therapy will be feasible, safe, and acceptable for individuals with PD and will promote positive clinical effects. The results of this feasibility study will be used to design a future definitive clinical trial.

There is strong evidence of the effectiveness of conventional (or usual) physical therapy to improve the motor and non-motor functions in individuals with PD [9, 12, 13]. However, to our knowledge, this will be the first randomized clinical feasibility trial that will investigate the safety, feasibility, and clinical outcomes of the Kinect games compared to conventional physical therapy in individuals with PD.

Previous studies have shown that interactive video games can improve motor and cognitive functions of individuals with PD [11, 12, 16]. Video games have emerged as a new low-cost virtual reality tool that can be potentially used in rehabilitation. The games can stimulate multi-directional displacements, weight transfer, controlled movements close to stability limits, a high number of repetitions, auditory and visual feedback, attention, planning, decision-making, sustained concentration, promoting motivation, and commitment in the tasks performed [11, 16]. However, commercial video games have not been developed specifically for individuals with neurological disorders, which could hinder their safety and feasibility to this population.

This study protocol is an innovative clinical feasibility trial regarding the evaluation of the feasibility, adherence, safety, acceptability, and effectiveness of the use of the Kinect games in comparison to conventional physical therapy in individuals with PD. The final results will be used to calculate the sample size needed for a potential larger multicenter trial. Our study may contribute to the understanding of the potential benefits of the interactive Kinect video game technology in rehabilitation of individuals with PD.

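### Non-serious adverse events count towards safety only if judged related to the intervention, so outside in-session falls and injuries the between-arm comparison can be skewed by attribution

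*Protocol article*

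**What the plan says.** Under Process outcomes, safety is to be assessed by "the proportion of participants who experienced intervention-related adverse events or any serious adverse event during the study period". The relatedness condition applies to non-serious events only. The same section defines an adverse event broadly and without reference to cause: "An adverse event was defined as any untoward medical occurrence, such as falls, joint and muscular pain, syncope, dizziness" and other conditions leading to hospital care or disability.

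The section Adverse effects of the intervention gives a second definition. For pain it builds in a cause and a duration: "Adverse events are defined as any sign of pain perceived by the participants due to the training protocol lasting for 2 days or more". For falls and injuries it goes by timing: "the occurrence of fall or injury to other body parts during training sessions will be considered as adverse effects".

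On blinding, Trial design states: "This study will be a single-blind, parallel-group, randomized controlled feasibility trial". Outcome measures and the randomization section describe the evaluators as blinded and ask participants not to tell them about their intervention. No section assigns the judgement of relatedness to anyone. The Background, the study objective and the Discussion all frame safety as a comparison; the Discussion asks whether the games are "feasible, safe, and acceptable for individuals with PD compared to conventional physical therapy".

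**The concern.** Randomisation balances background events between the arms. It does not balance opinions about what caused an event when those who hold the opinions can tell which treatment was given. Participants evidently know their intervention, since they are asked not to reveal it. Therapists lead group exercise in one arm and supervise individual video games in the other.

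The article itself supplies reasons why attribution could differ, and they point in opposite directions. The Discussion says commercial games were not developed for people with neurological disorders and that this might affect safety, which could raise attribution in the games arm. The Interventions section expects novelty and enjoyment to motivate that arm, which could lower it.

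A relatedness condition has a clear use in an uncontrolled study, such as the small pilot cited in the Background. Here the control arm already supplies the background rate. At stake is whether a difference in the safety proportion, or its absence, can be read as a difference in harm. The results are meant to inform a definitive trial.

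**Working it through.** The article gives no adverse-event rate, safety threshold or power for safety, so there is no stated figure to reproduce. The check has two parts.

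**1. Which events depend on attribution.** Non-serious events under each definition:

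| Event | Process outcomes rule | Adverse effects section |
|---|---|---|
| Pain | counts if judged related | counts if due to the training and lasting at least 2 days |
| Dizziness, syncope | counts if judged related | not listed |
| Fall outside sessions | counts if judged related | not listed |
| Fall or injury in a session | counts if judged related | counts by timing |

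Pain depends on attribution under either text. Dizziness, syncope and falls outside sessions depend on it under the first and are not listed in the second. In-session falls and injuries are largely free of it if the second text governs.

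**2. How far attribution could move the result.** From the document: 18 participants per group (Sample size). Everything else is assumed: true rate *p* of participants with a non-serious event, probability *a* that the event is called related, at most one such event per participant, and no serious events.

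Apparent rate = *p* × *a*.

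*Creating a difference.* Equal true rates, attribution 80% in one arm and 40% in the other:
- *p* = 20%: 0.20 × 0.80 = 16% v 0.20 × 0.40 = 8%, a spurious 8 points
- *p* = 40%: 32% v 16%, a spurious 16 points
- *p* = 60%: 48% v 24%, a spurious 24 points

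Reversing the attribution rates reverses the sign. Over *p* from 20% to 60% and attribution pairs of 70/30, 80/40 and 90/30, the spurious difference runs from 8 to 36 points. With equal attribution it is 0.

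*In counts.* At *p* = 40% and 80/40 attribution, the expected numbers are 18 × 0.32 = 5.8 v 18 × 0.16 = 2.9. An observed excess of at least 20 points means at least 4 participants (0.20 × 18 = 3.6). By exact binomial calculation its chance in the first arm is 40%, against 7% when attribution is 50% in both arms.

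*Hiding a difference.* True 60% v 30% with attribution 40% v 80%: 0.60 × 0.40 = 24% and 0.30 × 0.80 = 24%. A real doubling disappears.

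*Cost of counting every event.* Assume training-caused events in 5% v 25%, and independent background events in 40% of each arm. All-cause rates are 1 − 0.60 × 0.95 = 43% and 1 − 0.60 × 0.75 = 55%. The difference falls from 20 to 12 points. Its standard error at 18 per arm rises from √[(0.05 × 0.95 + 0.25 × 0.75)/18] = 11 points to √[(0.43 × 0.57 + 0.55 × 0.45)/18] = 17 points.

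**The case against.** The strongest reply is that the exposure is narrower than the outcome sentence suggests. A reader might infer that every non-serious event is open to attribution, including a fall while playing a jumping game. The adverse-effects section does not support that: it counts in-session falls and injuries by when they happen. This stands and limits the point.

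Three further inferences also go beyond the text.
- That participants decide the cause of their own pain. In "any sign of pain perceived by the participants due to the training protocol lasting for 2 days or more", the perceiving may attach to the pain alone.
- That whoever judges relatedness is unblinded. The randomization section has blinded therapists recording the measurements, although it does not expressly give them adverse events or causality. An article may leave that detail to the full protocol. Even so, a blinded recorder who relies on a participant's own account of cause does not make that account blind.
- That events at home or during follow-up would usually be called unrelated. Nothing in the document says how they would be classified.

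The illustration is also assumed throughout: the doubling is simply the 80:40 ratio carried through. It shows what the rule allows, and gives no evidence that attribution will differ.

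Finally, all-cause counting has its own weaknesses. Background events dilute a true difference by more than a trivial amount, as the last calculation shows, and the Background notes raised fall incidence in this disease. Participants who know their arm would still report their own symptoms. Both objections stand. They argue for showing both counts, and against relying on the related count alone for the comparison.

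**Conclusion.** The concern holds in a limited form. The stated safety rule makes the between-arm comparison of pain, dizziness, syncope and out-of-session falls depend on a causality judgement whose maker is not named, in a trial where only the evaluators are described as blinded. In-session falls and injuries are largely protected, provided the timing rule applies to the safety outcome. Serious events are unaffected.

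The direction and size of any bias are unknown; the 8 to 36 points above rest wholly on assumed rates. That participants and treating therapists know the arm is inferred from the interventions and from the request not to disclose, and is not stated outright.

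A reader might go on to infer an inflated false-positive rate or a faulty decision rule. The document does not support this: feasibility outcomes are presented descriptively, there is no formal sample size calculation, and no safety test or threshold is stated. What is at risk is a misleading descriptive comparison, which is cheap to prevent.

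**What to change.** In Process outcomes, base the between-arm safety comparison on the proportion of randomised participants with any adverse event, and separately with any fall, regardless of judged relation. Cover the whole study period to the 30-day follow-up in both arms. Show the intervention-related proportion beside it, by arm.

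Reconcile the adverse-event definitions in Process outcomes and in Adverse effects of the intervention, so that the same events are counted in both arms. It would also help to state who judges relatedness, by what criteria, and whether that person is blinded.

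The cost is a change of wording and an extra table column; no treatment changes. The downside is that background events raise both rates and can noticeably dilute a true difference, which is why the related count is kept alongside. Differential self-reporting by participants who know their arm would remain and should be acknowledged when the results are reported.
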